#### Content of the online multimodal rehabilitation programme

2.5.2.

The content of each of programme sessions will be based on scientific evidence that aims to address the symptoms of long COVID and, therefore, to improve quality of life of this patient population (13–17). The patients must adapt this intervention to their state of health, choosing the recommendations and advice that correspond to their symptoms and their specific health problems derived from this disease. Those recommendations or exercises that may cause some harm or discomfort to the participants must be discontinued immediately.

The multimodal rehabilitation sessions will consist of the following content:

##### Approach to neurological and neurocognitive symptoms

2.5.2.1.

Neurological symptoms are very prevalent in people with long COVID. These may include tiredness, sleep disorders, movement disorders, paraesthesia and cognitive deficits (35). The latter have been defined with the term “brain fog’”, which is characterised by feeling slow, confused and disoriented; having difficulties staying focused; presenting some forgetfulness; and the inability to find the correct word (36, 37). Currently, no specific treatment has been approved for this cognitive impairment in people with long COVID, although it has been determined that cognitive stimulation may be useful in some cases (38).

The content of this session will include: a description of the types of neurological symptoms typical of long COVID; treatment of neurocognitive symptoms; the benefits of performing cognitive stimulation exercises; personalised recommendations about what cognitive exercises can be practiced, and how and when to do it; and implementation of these treatments.

##### Approach to respiratory symptoms

2.5.2.2.

Long COVID often includes respiratory symptoms. The most common are usually shortness of breath, coughing and chest pain (39). Physiotherapy programmes focused on improving respiratory function can be useful in managing these persistent symptoms (40).

The content of this session will include: a description of the types of respiratory symptoms of long COVID; treatment of respiratory symptoms; the benefits of performing breathing exercises; personalised recommendations about what breathing exercises can be practiced, and how and when to do it; and implementation of these treatments.

Patients will be advised to use a pulse oximeter during these exercises. Whenever the patients experience any anomaly in the pulse oximeter values (resting oxygen saturation < 88%) (41) as well as any sensation of pain or pressure in the chest, they should automatically stop performing these exercises and consult what happened with the health professional during the sessions so that he/she can personalize the exercises to that specific person.

##### Approach to physical symptoms

2.5.2.3.

People with long COVID describe drastically reduced physical function. Hence, it becomes difficult or impossible for them to perform some ADL (42). Research on physical activity and long COVID is still insufficient, although there is scientific evidence for benefits in other pathologies with similar characteristics. Existing recommendations on physical activity and long COVID emphasise the importance of personalised care based on the symptoms that each person presents (43, 44).

The content of this session will include: a description of the types of physical symptoms of long COVID; treatment of physical symptoms; the benefits of physical activity; personalised recommendations about what activity and physical exercises can be practiced, and how and when to do it; and implementation of these treatments.

As with the breathing exercises, patients will be recommended to use a pulse oximeter while performing physical exercises, as well as to stop performing the exercises and consult a professional when noticing any abnormality in the values or any type of pain.

##### Recommendations for a healthy diet

2.5.2.4.

The Clinical Guide for Long COVID patient care of the Spanish Society of General and Family Physicians (SEMG) recommends considering food and diet in the management of this disease to fill possible nutritional deficiencies (16). Some nutrients such as folic acid, vitamin D, omega-3 fatty acids and vitamin B12, present in the Mediterranean diet, are involved in the proper functioning of metabolism and the immune system, so they could be useful in the recovery process of these patients (45, 46).

The content of this session will include: recommendations for a healthy diet based mainly on adherence to the classic Mediterranean diet.

##### Approach to sleep and rest disorders

2.5.2.5.

Sleep disorders (decreased sleep quality, daytime sleepiness, insomnia, sleep apnoea, nightmares, etc.) are common among the persistent symptoms of long COVID (47).

The content of this session will include: a description of the types of sleep disorders present in long COVID; information about different treatments for sleep disorders; a sleep hygiene programme; and recommendations for sleep and rest.

##### Managing emotional impact

2.5.2.6.

There is extensive research on the emotional impact on people with persistent symptoms of COVID-19. Anxiety, depression, post-traumatic stress disorder, mood fluctuations and sleep disorders are some of the consequences that long COVID can have on the mental health of people who have the disease (48).

The content of this session will include: a description of the emotional impact of long COVID; treatments aimed at addressing the emotional impact; recommendations about emotional management; an explanation of the first steps to take to meditate; and implementation of two meditation dynamics.

##### Behavioural activation and promotion of participation in the community

2.5.2.7.

The limiting persistent symptoms of long COVID, the consequences on mental health and the reduction in quality of life have a great impact on the organisation of the lives of people with this disease. They are limited in their ability to perform basic ADL, as well as their occupational, social and leisure activities in the community. This isolation is increased by feelings such as fear or uncertainty, barriers to accessing the health system or stigmatisation (7, 8, 49).

The content of this session will include: a description and examples of community health assets (HA); the benefits of using resources offered by the community itself; and personalised recommendations about what community resources can be used, and how and when to do it.

##### Compilation of important aspects, resolution of doubts, and farewell

2.5.2.8.

The last session, held the last week of the programme, will aim at collecting the most important therapeutic recommendations and at resolving doubts and questions that have arisen and that have not already been resolved in the previous sessions.

It is important to highlight that although each session is mainly aimed at addressing a specific type of symptomatology or impact on quality of life, the exercises described in the previous sessions will continue to be carried out and doubts that arise will be resolved. For example, in session 1, some cognitive stimulation guidelines will be explained, and cognitive stimulation exercises will be provided to patients to perform at home. In session 2, the patients will be able to express problems that have arisen when carrying out these exercises at home, and the therapist will even be able to carry out some other exercises to evaluate the progress of the patients with these symptoms.

### Outcomes and measures

2.6.

Data will be collected from questionnaires completed by the patients at the beginning and the end of the intervention. The assessors who administer the questionnaires will call and make an appointment with the patients following a list of first and last names arranged alphabetically and will not know the type of treatment given to each patient. Once the intervention is finished, an RA will contact the study participants and make an appointment to complete the questionnaires again. Hence, the effect that the intervention has had on the symptoms and quality of life will be evaluated. A follow-up will also be carried out after 3 months. The instruments that will be used are listed in Table 2. All assessments will last between 30 and 45 min per patient. If any of the patients experience cognitive fatigue and feel unwell due to the long duration of the assessments, they may be stopped and continued another day.

**Table 2 tab2:** Study variables and measurement instruments.

Instrument	Assessment area
Gender, age, marital status, education, household, occupation	Sociodemographic
Contraction of COVID-19, number of residual symptoms and their severity	Clinical variables
36-Item Short Form Health Survey Questionnaire (SF-36) (50, 51)	Quality of life
Montreal Cognitive Assessment (MoCA) (52–54) Memory Impairment Screen (MIS) (55, 56) Semantic Verbal Fluency Test (Animals) (57, 58) Stroop Colour and Word Test (59)	Cognitive variables
Sit to stand test 30 s (60)	Functional physical variables
Hospital Anxiety and Depression Scale (HADS) (61)	Affective state
Insomnia Severity Index (ISI) (62)	Sleep quality
International Physical Activity Questionnaire (IPAQ-SF) (63)	Physical activity
Self-efficacy scale (64) Health Literacy Europe Questionnaire (HLS-EUQ16) (65) Patient Activation Measure Questionnaire (PAM) (66)	Personal constructs
Likert scale	Satisfaction with the program

#### Primary outcome

2.6.1.

The main variable will be quality of life, evaluated through the SF-36 (67). This questionnaire measures eight dimensions of health: physical function, physical role, aches and pains, general health, vitality, social function, emotional role and mental health; it also includes a declared health evolution item. The eight dimensions define two main components of health: a physical summary component and a mental summary component. In them, scores above or below 50 indicate, respectively, a better or worse state of health than the mean of the reference population. Items are scored on a Likert-type scale from 1 to 3.5 or 6, depending on the type of item. The total score of the eight scales ranges from 0 to 100, with higher scores indicating better health. The validated Spanish version of the questionnaire will be used (68).

#### Secondary outcomes

2.6.2.

##### Sociodemographic variables

2.6.2.1.

Age, gender, marital status, education, household and occupation will be collected.

##### Clinical variables

2.6.2.2.

The date of contracting COVID-19 and the number and severity of persistent symptoms measured by Visual Analog Scale (69) will be collected. Persistent symptoms include: low-grade fever (37–38°C), fever (> 38°C), chills without fever, headaches, dizziness, tiredness or fatigue, sore throat, cough, dyspnoea, loss of smell and/or taste, blurred vision and other eye problems (dry eyes, increased dioptres, conjunctivitis), bruising, hair loss, tachycardia, myalgia, joint pain, orthostatic hypotension, chest pain, back pain (cervical, thoracic and/or lumbar), gastrointestinal symptoms, urinary symptoms (overactive bladder, infections), neurological symptoms (spasms, tingling, etc.), cognitive impairment (memory loss, reduced attention, mental fog), altered menstrual cycle, loss of libido or erectile dysfunction, and other symptoms that the participants consider persistent (70–72).

##### Cognitive variables

2.6.2.3.

The official Spanish version of the Montreal Cognitive Assessment (MoCA) (52–54) will be used to assess the presence of cognitive impairment in the participants of this study. This is a test with adequate internal consistency (Cronbach’s alpha = 0.76) and assesses six cognitive domains: memory, visuospatial capacity, executive function, attention/concentration/working memory, language and orientation. Of the total score of 30 points, a correction of one point can be made in the case of subjects with less than 12 years of schooling. The cut-off point of this scale for the detection of mild cognitive impairment in its original version is 26. This test has been used in previous research to assess cognitive impairment in people with long COVID (73, 74).

The presence of short-term memory impairment will be measured by using the Spanish version of the Memory Impairment Screen (MIS). This short test assesses the presence of memory disturbances by testing free recall (without clues) or selective recall (with semantic clues) of four words. Dementia screening has adequate interobserver (0.85) and test–retest (0.81) reliability. One point is awarded per word recalled with the help of semantic clues, and two points per word obtained by free recall. The total score ranges from 0 to 8, with a score of ≤4 points indicating possible deterioration (55, 56).

The Semantic Verbal Fluency Test (Animals) will be used to assess whether verbal fluency is affected. The test–retest reliability is 0.68. This test consists of counting the number of correct words within the ‘Animals’ category, reproduced for 1 min. Normally, a healthy person will be able to reproduce about 16 words per minute (57, 58).

The Stroop Colour and Word Test will be used to assess processing speed. This test consists of three phases spread over three different pages. On the first page, the words “red”, “green” and “blue” are printed in black ink, randomly repeated in columns. On the second page, the element “XXXX” appears repeatedly and in columns, printed in red, green or blue ink. On the third page, the words “red”, “green” and “blue” are printed in red, green or blue, but the words do not match the colour in which they are printed. The patient must, by columns, read words or name the ink colours as quickly as possible for 45 s (75, 76). There are scales corrected for age (7–80 years) to calculate the total score for this test. In the various existing versions, this test has shown consistent reliability, obtaining indices of 0.85, 0.81 and 0.69 for the three direct scores (59).

##### Functional physical variables

2.6.2.4.

The Sit to Stand Test will be used to measure the strength and endurance of the lower limbs (60). The 30-s version of this test will be used; it is specifically designed to detect respiratory diseases (58). It evaluates endurance at high power or speed in terms of muscular endurance or strength by recording the number of times a person can stand up and sit down completely in 30 s. This instrument had good test–retest reliability (0.84 < R < 0.92). The 30-s Sit to Stand Test has been translated into Spanish and used in patients with COVID-19 (77).

##### Affective variables

2.6.2.5.

The affective state will be evaluated by using the Hospital Anxiety and Depression Scale (HADS) questionnaire (61). This is a self-report-based scale designed to screen for depression and anxiety disorders in primary care settings. It consists of 14 items that assess symptoms of anxiety and depression (HADS-A and HADS-D, respectively), each item corresponding to a 4-point scale (0–3), with a score range from 0 to 21 for anxiety symptoms and depression symptoms. Higher scores indicate more severe symptoms. To facilitate its use in international trials, this test has been translated into multiple languages, including Spanish (78).

##### Sleep quality

2.6.2.6.

The Insomnia Severity Index (ISI) will be used to measure the participants’ sleep quality (60). This is a self-report that measures the patient’s perception of nocturnal and daytime symptoms of insomnia: difficulty falling asleep or staying asleep, waking up early in the morning, satisfaction with the current sleep pattern, interference with the daily functioning, perceived impairment attributed to sleep deprivation and level of distress or worry caused by the lack. This scale has seven items, each of which is scored from 0 to 4. The total score ranges from 0 to 28, with a higher score indicating more severe insomnia. The Spanish version of the ISI (79) has shown adequate internal consistency (Cronbach’s alpha = 0.82). This test has already been used in other studies about long COVID (80).

##### Personal constructs

2.6.2.7.

Self-efficacy will be measured by using the Self-Efficacy Scale-12 (64). The original scale consists of 17 items that are scored using a 5-point Likert scale. Woodruff and Cashman (81) derived a factor structure representing the three aspects underlying the scale: willingness to initiate the behaviour (“Initiative”), willingness to strive to complete the behaviour (“Effort”) and persistence in the face of adversity (“Persistence”). These are the three factors that this scale evaluates. Five items have been excluded due to low item-remainder correlations and ambiguous wording, resulting in a 12-item version (GSES-12). The total scale has a Cronbach’s alpha of 0.69, and its internal consistency is 0.64 for “Initiative”, 0.63 for “Effort” and 0.64 for “Persistence” (82).

The Health Literacy Europe Questionnaire (HLS-EUQ16) will be used to measure the health literacy of the participants (79). This is defined as the motivation of the population, their knowledge and their individual capacity to understand and make decisions regarding the promotion and maintenance of their health. The questionnaire consists of 16 items, each scored from 1 (very easy) to 4 (very difficult). The total score is obtained by adding the scores of all the items. The final score can be converted into a dichotomous answer: very difficult and difficult = 0; easy and very easy = 1. Poorer health literacy is indicated by higher scores. The official Spanish version presents high consistency (Cronbach’s alpha = 0.982) (83).

The activation of the patient about his own health will be measured by using the Patient Activation Measure (PAM) (66). This tool evaluates the skills, knowledge and confidence perceived by the patient when carrying out health self-management activities. It comprises 13 items that are evaluated on a Likert-type scale from 1 (totally disagree) to 4 (totally agree). The resulting score ranges from 13 to 52, with higher scores indicating higher levels of activation. There is only one official version in Spanish that applies to patients with chronic disease. It has a reliability of 0.98 and a parametric discrimination index of 6.64 (84).

##### Personal satisfaction with the content and tools

2.6.2.8.

In the last assessment, using a Likert-type scale from 0 to 10, the level of satisfaction both with the content of the program and with the tools used for its development will be assessed.

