### Data collection and monitoring

2.4.

A RA will collect the data, and another will enter and encode the identification data. All RAs handling the data will be blind to patient allocation, as will the RA performing outcome assessment and data analysis. All the information collected will be treated in accordance with the provisions of the current legislation on the protection of personal data.

Any serious unexpected adverse event or result will be discussed by the trial management committee (the authors of this protocol). There are no plans to discontinue or modify the interventions, to improve adherence or to promote participant retention. The committee will monitor enrolment, treatment, attrition rates and any concerns related to the study. The reasons for abandonment will also be recorded.

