### Intervention

2.5.

Patients assigned to the control group will follow the treatment as usual provided by their GP.

Patients assigned to the intervention group will follow the treatment as usual provided by their GP and will participate in a multidisciplinary online multimodal rehabilitation programme. The programme will be aimed at addressing the symptoms of people with long COVID and improving their quality of life. This objective will be pursued by providing exercises and therapeutic recommendations related to physical activity, respiratory rehabilitation, cognitive rehabilitation, diet, sleep hygiene, use of community resources and emotional management.

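### The programme-satisfaction item, collected in the last assessment as part of the blinded battery, reveals the arm to staff whom the protocol requires to be blind

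*Protocol article*

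**What the plan says.** Section 2.6.2.8 sets the timing and scale of the item, "In the last assessment, using a Likert-type scale from 0 to 10", and its object: "the level of satisfaction both with the content of the program and with the tools used for its development will be assessed". It names no arm, no separate collector and no separate form.

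Section 2.6 makes the item part of the common battery. It says "The instruments that will be used are listed in Table 2", and the last row of that table is a Likert scale for satisfaction with the programme. The same section says that the assessors who give the questionnaires "will not know the type of treatment given to each patient".

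Section 2.4 sets the masking more widely: "All RAs handling the data will be blind to patient allocation, as will the RA performing outcome assessment and data analysis". Section 2.3 adds a safeguard by asking participants not to tell other researchers which group they are in.

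Section 2.5 describes the comparator: "Patients assigned to the control group will follow the treatment as usual provided by their GP". Controls are given no videoconferences and no Moodle platform.

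**The concern.** Participants cannot be blinded in this trial, and Section 2.3 says so. What masking there is rests on the assessors, the data handlers and the analyst. The protocol asks participants to keep their allocation to themselves and then schedules a question whose answer discloses it.

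Two things are at stake. The first is the assessor's neutrality on tests that depend on prompting, timing or counting: MoCA, MIS with its cued and free recall, verbal fluency, Stroop and the 30-second sit-to-stand. The second is the masking of data entry and analysis. If the item sits in the ordinary dataset, the trial could not securely report that those who handled and analysed the data were blind.

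**Working it through.** No figure in the protocol bears on this point, so the check consists of reading the provisions together.

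1. **Who can answer.** By Section 2.5, only the intervention arm receives programme content and tools. A substantive rating therefore identifies an intervention participant. A reply that there was no programme identifies a control.

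2. **Who collects it.** By Section 2.6 and Table 2, the item belongs to the battery given by blinded assessors. If the assessor puts the item to everyone, the answers show the arm. If the assessor puts it only to intervention participants, the assessor must be told in advance who they are. Either route conflicts with Sections 2.4 and 2.6.

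3. **Who sees the data.** Suppose the assessor never sees the answer, for example because the patient fills in the form alone. The value still has to be entered and stored. A 0 to 10 score that is present in one group and blank or not applicable in the other decodes the groups, even if they are labelled only A and B. A single blank could be an ordinary missing value, but the pattern over the column could not. This step does not depend on the order of questions.

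4. **When it happens.** Section 2.6 describes assessments before the intervention, at its end and 3 months later. Read plainly, the last assessment is the 3-month follow-up, so baseline and post-intervention ratings were made before the item was asked.

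5. **Whether test ratings can be affected.** There are three cases:
   - The item comes after all tests in a single session: that participant's tests are already scored, and no later rating exists to bias.
   - The item comes before some tests: the assessor rates those tests knowing the arm.
   - The session is stopped and resumed another day, which Section 2.6 allows for fatigued patients: tests done after the item are exposed if the item fell in the first part.

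   The protocol does not say which case applies.

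6. **Which outcomes are exposed.** Assessor knowledge bears on the performance tests named above, all of them secondary. The primary outcome, SF-36, is reported by patients who already know their arm, so the assessor's knowledge does not alter it. Loss of analyst masking is not confined to particular outcomes.

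**The case against.** The strongest reply is that the protocol never says in so many words that the blinded assessor asks, reads or enters this item. Section 2.6 also speaks of questionnaires that patients complete. A condensed article commonly leaves battery order and form handling to the full protocol. Satisfaction is listed last both in Table 2 and in the section order, which may suggest that it is asked last.

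Part of this stands. A reader might infer that the 3-month performance tests will be rated with knowledge of the arm. The document does not support that, because the order is unstated and an item asked last in a single session could not affect tests already scored.

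The reply does not remove the conflict. The finding is not that a safeguard is missing. The text places the item in a battery that it says is given blind. Neither the table order nor the section order is stated to be the order of administration. Asking the item last also leaves data entry and analysis exposed (step 3).

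A reader might also infer an analysis error: the item appears under secondary outcomes, Section 2.7 applies mixed models to the secondary variables, and a one-off rating in one arm has no between-group change to model. That reading is too literal. Section 2.6.2 also lists age, gender, marital status and education, so the heading is a list of collected variables rather than of model endpoints. It is not a separate error.

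**Conclusion.** The point holds as a conflict between the placing of this item and the masking promised in Sections 2.4 and 2.6. Followed as written, the plan can reveal the arm of every participant who attends the last assessment: intervention participants by their rating, controls by its absence. That counts people unmasked and is not an effect size. The size of any resulting bias cannot be estimated from the document.

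The breach of data-handler and analyst masking holds whatever the order of questions, provided the item is stored with the other outcomes. Biased test ratings are conditional on the item coming before the tests or on a split session. They would be limited to secondary performance tests at the last assessment. Assessor knowledge does not touch SF-36 or the earlier visits.

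The conclusion assumes that the last assessment is the 3-month follow-up. If the post-intervention visit were meant, assessor ratings at the later follow-up would be exposed too, so the term should be made explicit.

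**What to change.** Take the item out of the blinded battery and state in Sections 2.6 and 2.6.2.8 that:

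- it is asked of intervention participants only, after all other measures of the last assessment are complete, including any part carried over to another day;
- it is collected by a self-completed form, for which the Moodle platform already exists in that arm, or through the research assistant who communicates allocation under Section 2.3 and so already knows it;
- it is kept out of the blinded dataset until the efficacy analysis is finished;
- it is reported descriptively for the intervention arm;
- the last assessment means the 3-month follow-up, if that is what is intended.

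Simply moving the item to the end of the session would be simpler and would protect the test ratings in a single sitting, but it would not protect data entry or analysis.

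The cost is one short form, a few sentences and possibly a slightly lower response to this item. Because the item is collected only at the final visit, no earlier measurement has to change.
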